**Methods:**

Women will be recruited during outpatient maternity checkups at four perinatal care institutions in Japan. We will recruit women at less than 30 weeks of gestation with a pre-pregnancy body mass index ≥ 25 kg/m^2^. The women will be randomly assigned to an intervention or non-intervention group. The intervention will involve using data (weight, body composition, activity, sleep) measured with IoT devices (weight and body composition monitor, activity, and sleep tracker), meal records, and photographs acquired using a mobile application to automatically generate advice, alongside the use of a mobile application to provide articles and videos related to obesity and pregnancy. The primary outcome will be the ratio of change in body weight (%) from pre-pregnancy to 12 months postpartum compared to before pregnancy.

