### Intervention

The intervention will be initiated on the day consent is provided during pregnancy to 1 year postpartum. The IoT intervention for this trial is defined as (1) automatically generated advice based on data (weight, body composition, activity, sleep) measured using IoT devices and meal records and photographs recorded with a mobile application (Calo Mama Plus Pregnant woman Course®) and (2) provision of articles and videos related to obesity and pregnancy via a mobile application.

The following IoT devices will be distributed to all participants: body composition monitor and scale (HBF-227t, Omron Healthcare Inc., Tokyo) and fitness tracker (Fitbit Inspire®, Fitbit Inc., San Francisco, CA).

Participants in the intervention group will use a mobile application (Calo Mama Ninsanpu Plus®). The target weight 1 year postpartum has been set at 93% of the pre-pregnancy weight. Participants will monitor themselves daily to the extent possible using the IoT devices (weight and body composition monitor, activity, and sleep tracker) and by entering meal records and photographs into the mobile application.

The mobile application (Calo Mama Plus Ninsanpu Course®) has the following four functions: 

It automatically generates personalized advice based on conditions during and after pregnancy. Personalized advice is generated automatically based on data (weight, body composition, activity, and sleep) measured with the IoT devices and meal records and photographs recorded by the mobile application, alongside considering how far long in the pregnancy the participant is or the number of weeks postpartum.It provides articles based on the number of weeks of pregnancy or postpartum. The articles are delivered once or twice a week on themes that match the number of weeks of pregnancy or postpartum.It provides breastfeeding advice. After delivery, advice on breastfeeding is provided that reflects the breastfeeding status (number of times the participant recorded breastfeeding and amount of milk).It plots the body weight during pregnancy. Weight measurements during pregnancy are plotted on a graph and advice on weight changes based on the pre-pregnancy BMI is provided.

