All participants will measure their blood pressure at home over 3 days at 6, 12, and 24 months postpartum. The HBF-227t sphygmomanometer manufactured by OMRON Healthcare Co. will be used. Measurements will be taken twice a day in the morning (within 1 h of waking up, after urinating, before taking any medication, and after resting for 1–2 min) and before going to sleep (after resting in the sitting position for 1–2 min). In principle, two measurements will be taken each time.

Table 1 shows the schedule for the trial.

**Table 1 Tab1:** Study timeline for intervention and data collection

		Trial duration								
		Obtain consent		Intervention						Completion
Pregnancy, postpartum			Start of trial	During pregnancy	Delivery	1 month postpartum	6 weeks postpartum	6 months postpartum	12 months postpartum	24 months postpartum
	Obtain consent	×								
	Registration	×								
Regular management	Regular medical care, guidance (maternity checkups)Regular health guidance			○ (maternity checkup→→		○ (1-month postpartum checkup)				
Measure at home	Weight, body composition		○			○		○	○	○
	Activity, sleep		○					○	○	○
Blood pressure	Blood Pressure							○	○	○
Postal checkups	Postal checkup (blood glucose, HbA1c, etc.)							○	○	○
App intervention	Weight, activity, sleep		●	→→→→→→→			●→→→	→→→→→→	→	
	Meal photos		●	→→→→→→→			●→→→	→→→→→→	→	
Mother and Child Handbook	Maternity checkup data (urine test, blood pressure, weight)					○				
	Pregnancy outcome data					○				
Questionnaire	Background, lifestyle		○							
	EPDS		○			○				
	Breastfeeding status					○		○	○	
	Breastfeeding process					○				
	Behavioral changes (attitude, knowledge)		○					○	○	
	User-friendliness of devices							○	○	
	Desire to continue using IoT after end of study								●	

○ Both groups, ● intervention group only

If there are missing data, the research coordinator at each site and trial secretariat will contact the participants. Data from the weight and body composition monitor, activity and sleep tracker, and online questionnaires will be stored on the Internet server. The data file will be secured with a password, and access to information will be limited to designated members such as the researchers and the trial secretariat. Paper-based documents such as consent forms will be stored at each site.

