### Primary outcome

The primary outcome will be the ratio of change in body weight (%) from pre-pregnancy to 12 months postpartum.

The pre-pregnancy weight will be self-reported, as weights reported by obese individuals have been reported to differ only slightly from actual measurements. The body weight at 12 months postpartum will be directly retrieved from the smartphone application as measured by the device.

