#### Health outcomes

✓ Pregnancy outcomes (gestational age at delivery, cesarean section rate, preterm birth rate, excessively large baby rate, birth height, birth weight, SD value, large-for-gestational-age rate, pregnancy-induced hypertension rate, gestational diabetes rate, etc.)Maternity checkup and pregnancy outcome data will be collected from the Maternal and Child Health Handbook.✓ Weight gain during pregnancy (kg)Calculated as: (weight immediately before delivery retrieved from the Maternal and Child Health Handbook)—(pre-pregnancy weight).✓ Change in weight from before pregnancy to 1, 6, 12, and 24 months postpartum (kg)✓ Rate of change in weight from before pregnancy to 1, 12, and 24 months postpartum (%)

The postpartum weights will be directly retrieved from the smartphone application as measured by the device.✓ Percentage of participants who will reach the target weight (at 6, 12, and 24 months postpartum) (%)A participant will be considered to have reached the postpartum target weight if/when their body weight declines to 93% of the weight before pregnancy.✓ Change in body fat ratio from 1 month postpartum to 6, 12, and 24 months postpartum✓ Percentage of participants with hypertension (excluding those having been diagnosed before pregnancy)The mean of the two blood pressure readings taken at home in the morning and before going to bed will be used. If only one blood pressure reading is taken, that value will be used. Hypertension is defined as a 3-day mean of ≥ 135 mmHg and/or ≥ 85 mmHg.✓ Percentage of participants with impaired glucose tolerance or diabetes (at 6, 12, and 24 months postpartum)Postpartum impaired glucose tolerance is defined as fasting blood glucose ≥ 110 mg/dl and ≤ 125 mg/dl or HbA1c ≥ 6.0% and ≤ 6.4% in the at-home blood samples. Diabetes is defined as a fasting blood glucose level of ≥ 126 mg/dl or HbA1c is ≥ 6.5%.✓ Percentage of participants with EPDS ≥ 9 (start of the study and at 1 month postpartum)

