### Sample size

Assuming a -2% weight change at 12 months postpartum compared to before pregnancy in the non-intervention group, the trial was designed to detect whether the IoT/mobile application intervention would result in a -5% weight change at 12 months postpartum. To conduct a two-sided test with a standard deviation of 8% and significance level of 5% at 80% power, 226 participants in both groups are needed. Assuming loss of approximately 20% of participants from exclusion or drop-out, the target number of registrations is set to 270 women.

There are 6,000 deliveries each year at the trial institutions. If 10% of the women are obese, the total number comes to 600 per year. As pregnant women at up to 30 weeks of gestation are eligible for registration, 250 pregnant women at up to 30 weeks of gestation who have already visited the outpatient maternity clinic for checkups and 250 pregnant women who newly visit during the 5-month registration period will be eligible. Hence, it is expected to be possible to register the target number of participants.

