### Analysis of secondary outcomes

For continuous variables, the mean and 95% confidence interval will be calculated for each group and t-tests will be used for group comparisons. For discrete variables, the number, proportion, and 95% confidence interval for the proportion will be calculated for each group, and the chi-square test will be used for group comparisons.

Regarding the breastfeeding proportion, ≥ 80% breastfeeding (daily milk amount ≤ 125 ml at 1 month postpartum and ≤ 164 ml at 6 months postpartum) will be used for between-group comparisons. Regarding the dietary items, the means and 95% confidence intervals will be calculated for each item at each time point (at the start of the study and 6 and 12 months postpartum) in the intervention group. The same analysis will be performed to analyze changes from the start of the study to 6 and 12 months postpartum.

For device usage, the use of activity tracker meters, wearing the weight/body composition monitor, and performance of measurements with the weight/body composition monitor at each time point (6 and 12 months postpartum) will be summarized and compared between the groups. In the group that will not use the devices at the beginning of the study, the number, proportion, and 95% confidence interval for the proportion will be calculated for participants who started using the devices at 6 and 12 months postpartum.

Regarding mobile application use, the mean and 95% confidence intervals will be calculated for the number of logins and viewing time at each time point in the intervention group (at 6 and 12 months postpartum). For uploading of meal images (at 6 and 12 months postpartum) and viewing of breastfeeding videos (during pregnancy and at 6 weeks postpartum), the number, proportion, and 95% confidence interval will be calculated for the intervention group.

Regarding the continuation of the intervention program (at 6 and 12 months postpartum), the number, proportion, and 95% confidence interval will be calculated for the intervention group.

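### The unadjusted t-test on total pregnancy weight gain leaves in variation from before study entry, which weights already collected in both arms could remove

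*Protocol article*

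**What the plan says.** All places are in the protocol article.

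- **Aim.** The Discussion part of the Abstract names suppression of weight gain in pregnancy as something the trial seeks to show. The main Discussion gives it as the first reason for starting in pregnancy.
- **Start of intervention.** Under Intervention: "The intervention will be initiated on the day consent is provided during pregnancy to 1 year postpartum".
- **Entry.** The Abstract says "We will recruit women at less than 30 weeks of gestation", and Participants sets no lower limit. Sample size counts on 500 eligible women, half of them described as "250 pregnant women at up to 30 weeks of gestation who have already visited the outpatient maternity clinic for checkups".
- **Outcome.** Under Health outcomes, weight gain during pregnancy in kg is "weight immediately before delivery retrieved from the Maternal and Child Health Handbook", less the pre-pregnancy weight. Primary outcome states: "The pre-pregnancy weight will be self-reported".
- **Analysis.** For continuous secondary outcomes, "t-tests will be used for group comparisons". No covariate is named.
- **Weights available at entry.** Table 1 lists "Maternity checkup data (urine test, blood pressure, weight" from the Mother and Child Handbook for both groups. Data collection also has every participant weigh herself at the start of the study.

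**The concern.** A woman who consents at 28 weeks has already put on part of her pregnancy weight before either arm can affect it. The outcome counts that weight, together with any error in the reported starting weight, and the t-test removes neither. Both widen the spread against which the difference between arms is judged.

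At stake is the precision of the test that speaks most directly to the pregnancy part of the aim. A real effect after entry could be missed and then read as no suppression of weight gain, when a baseline that would sharpen the comparison is already on file.

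**Working it through.** **1. The plan's own figure.** A difference of 3 points (-5% against -2%), SD 8%, two-sided 5% and 80% power give 2 × (1.96 + 0.8416)² × (8/3)² = 111.6, so 112 per arm by the normal formula. The t-test version gives 112.6, so 113 per arm and 226 in total, which matches Sample size. That figure is for weight at 12 months postpartum. The article gives no SD, effect, weekly gain or distribution of entry weeks for pregnancy weight gain, so every power figure below rests on assumptions.

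**2. Where the noise sits.** Let D be the last weight before delivery, E the weight at entry and P the reported pre-pregnancy weight.

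D − P = (D − E) + (E − P)

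The intervention can move only D − E. The variance of the outcome is Var(D − E) + Var(E − P) + 2 Cov(D − E, E − P). The extra terms cost power unless the correlation between gain before and after entry is at or below −SD(E − P) / [2 SD(D − E)].

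**3. Power if gain before entry is independent noise.** Assume the effect is 0.375 SD of D − E, with 113 per arm. If a share f of the total variance comes from E − P, power = Φ(0.375 × √(1 − f) × √(113/2) − 1.96).

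| f | Power | Per arm for 80% |
|---|---|---|
| 0 | 0.80 | 112 |
| 10% | 0.76 | 125 |
| 20% | 0.71 | 140 |
| 30% | 0.66 | 160 |
| 40% | 0.59 | 187 |
| 50% | 0.51 | 224 |
| 60% | 0.43 | 280 |

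**4. Simulation with one average gain rate.** Assumptions: mean gain 0.2 kg/week, effect 0.08 kg/week after entry, delivery at 40 weeks, SD of total gain about 6 kg, report error SD 1.5 kg, entry weight measured without error, 113 per arm.

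| Entry weeks | t-test, total gain | t-test, gain from entry | Gain from entry, adjusted for gain before entry and gestation at entry |
|---|---|---|---|
| 8–30 | 0.51–0.55 | 0.79–0.95 | 0.81 to over 0.99 |
| 20–30 | 0.30–0.32 | 0.66–0.95 | 0.66 to over 0.99 |

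Hand check of the first column: mean entry at 19 weeks gives an effect of 0.08 × 21 = 1.68 kg. With SD 6.1 kg, Φ(1.68 / (6.1 × √(2/113)) − 1.96) = 0.54. For mean entry at 25 weeks the effect is 1.20 kg and the power 0.32. Most of the fall between the rows of that column comes from the later start, which no change of baseline would undo. Only the gap across a row belongs to the outcome definition and its analysis.

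**5. Simulation with two gain rates.** Assumptions: 0.12 kg/week to 20 weeks and 0.32 after, between-woman SDs 0.10–0.20 and 0.20–0.25, report error SD 0–2 kg, weighing error SD 0.5 kg, delivery at about 39 weeks, entry at 8–30 weeks, effect 0.08 kg/week, 108 per arm (270 × 0.8 / 2). At these rates a 28-week entrant has 0.12 × 20 + 0.32 × 8 = 4.96 kg of an expected 8.48 kg behind her, or 58%.

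- Correlation 0 to 0.6 between early and late gain: 0.29–0.76 for total gain by t-test, against 0.66–0.91 for gain after entry. The smallest gap was about 12 to 14 points. Elsewhere it reached 0.35 against 0.84.
- Correlation −0.6 with no report error: 0.81–0.97 for total gain, against 0.74–0.93 for weekly gain after entry and 0.79–0.96 for gain after entry adjusted for weeks of exposure. There is no loss here.
- Total gain adjusted for entry weight and gestational age at entry: 0.75–0.96, equal to or better than the alternatives in nearly every scenario.

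**The case against.** Four points can be made for the plan as written.

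*Randomisation deals with it.* A reader might infer that counting gain from before entry biases the comparison. It does not. Gain before entry has the same expectation in both arms, so the difference in total gain estimates the same quantity as the difference in gain after entry. This takes the site-and-day allocation described under Allocation as valid randomisation, which is a separate question. The objection stands: the issue is precision.

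*Total gain is the quantity of interest.* Background ties excessive gain in pregnancy to postpartum weight retention, the application's advice refers to pre-pregnancy BMI, and the primary outcome also starts from pre-pregnancy weight. This stands too, and it argues against replacing the outcome. It does not argue for leaving the test unadjusted.

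*The outcome is secondary and was never powered.* True. The formal objective, the primary outcome and the sample size all concern 12 months postpartum. That limits the weight of the point without removing it, because the aim is stated and the data are in hand.

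*The loss may be small.* It may. At a 10–20% share before entry it is about 4 to 9 points. If women who gain much early gain less later, which advice on weight could bring about, it can vanish.

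**Conclusion.** The point holds as one of efficiency for one secondary outcome. The outcome includes gain that the intervention could not influence, plus self-report error, and the stated t-test leaves both in. The estimate is not biased by this, and the primary outcome is not affected.

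It is tempting to say that the test loses much of its power. The documents do not support that as a fact, because they give none of the inputs needed. Under independent noise the loss is about 4 points at a 10% share and 37 points at 60%. Across the simulated scenarios it runs from none (negative correlation, accurate reports) to more than 40 points (positive correlation or late entry). A sizeable loss is plausible if many women enter in mid-pregnancy, but it remains conditional on those assumptions.

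Because the remedy is nearly free and the outcome bears on a stated aim, the change is worth making.

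**What to change.** Keep weight gain during pregnancy as defined under Health outcomes. In Analysis of secondary outcomes, replace the t-test for this outcome with a linear model (analysis of covariance) of total gain on arm, weight at study entry, pre-pregnancy weight and gestational age at entry. With entry weight and pre-pregnancy weight both in the model, the arm coefficient and its standard error are the same whether the response is D, D − P or D − E. The choice of starting point then no longer matters for the test.

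Name one source of entry weight for all women, for example the handbook weight from the checkup on the day of consent. Using the home scale only where that value is missing would mix instruments within one covariate. Report gain from entry to delivery by arm as a supporting figure.

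Do not divide by, or adjust for, weeks from entry to delivery. That interval ends at delivery and so depends partly on events after randomisation, whereas gestational age at entry is fixed beforehand.

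The cost is a change of wording and one model, using data already collected in both arms. The small downside is a model-based estimate in place of a simple difference in means; the unadjusted means can still be shown.

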**Fig. 2 Fig2:**
[figure not shown]
Study timeline for intervention and data collection

If a participant withdraws her consent, cannot be contacted because of a move or hospital change, and the next pregnancy will continue for 14 weeks or more after delivery, participation will be discontinued. No criteria have been set for allocation modification.

### Data collection

All study participants must weigh themselves once at the start of the study and at 1, 6, 12, and 24 months postpartum and track their activity and sleep patterns for 1 week at the beginning of the study and at 6, 12, and 24 months postpartum. Body weight will be measured once a day in the morning using the weight and body composition monitor. Activity and sleep will be measured using an activity and sleep tracker, which will be worn on the non-dominant arm at all times, even during sleep, except during recharging (once every 5 days).

All participants will complete online questionnaires at the beginning of the study and at 1, 6, and 12 months postpartum. If any data are lacking, they will be collected from the medical records. Details of the questionnaires developed for this study are as follows (supplementary file):

Background and lifestyle (at the start of the study): items related to pregnancy and delivery history, medical history, family history, and exercise and dietary habits.Edinburgh Postnatal Depression Score (EPDS) (start of study, 1 month postpartum) [22].Breastfeeding status (intensity, duration) questionnaire (1, 6, 12 months postpartum).Breastfeeding process questionnaire (1 month postpartum).Behavioral changes (attitude, knowledge) (6, 12 months postpartum).User-friendliness of devices, barriers to lifestyle improvements and behavioral changes, areas for improvement, etc. (6, 12 months postpartum) (both groups).Desire to continue using the IoT devices after the trial ends (12 months postpartum) (intervention group only).

All participants will have blood samples taken at home via postal self-checkups at 6, 12, and 24 months postpartum to measure HbA1c, fasting glucose, total protein, albumin, AST, ALT, γ-GTP, total cholesterol, HDL cholesterol, triglycerides, urea nitrogen, creatinine, and uric acid. To collect blood samples, the trial secretariat will send test kits to the participants for postal self-checkups. Results of the postal self-checkups will be returned by mail to the participants within 6 weeks.

All participants will measure their blood pressure at home over 3 days at 6, 12, and 24 months postpartum. The HBF-227t sphygmomanometer manufactured by OMRON Healthcare Co. will be used. Measurements will be taken twice a day in the morning (within 1 h of waking up, after urinating, before taking any medication, and after resting for 1–2 min) and before going to sleep (after resting in the sitting position for 1–2 min). In principle, two measurements will be taken each time.

Table 1 shows the schedule for the trial.

**Table 1 Tab1:** Study timeline for intervention and data collection

		Trial duration								
		Obtain consent		Intervention						Completion
Pregnancy, postpartum			Start of trial	During pregnancy	Delivery	1 month postpartum	6 weeks postpartum	6 months postpartum	12 months postpartum	24 months postpartum
	Obtain consent	×								
	Registration	×								
Regular management	Regular medical care, guidance (maternity checkups)Regular health guidance			○ (maternity checkup→→		○ (1-month postpartum checkup)				
Measure at home	Weight, body composition		○			○		○	○	○
	Activity, sleep		○					○	○	○
Blood pressure	Blood Pressure							○	○	○
Postal checkups	Postal checkup (blood glucose, HbA1c, etc.)							○	○	○
App intervention	Weight, activity, sleep		●	→→→→→→→			●→→→	→→→→→→	→	
	Meal photos		●	→→→→→→→			●→→→	→→→→→→	→	
Mother and Child Handbook	Maternity checkup data (urine test, blood pressure, weight)					○				
	Pregnancy outcome data					○				
Questionnaire	Background, lifestyle		○							
	EPDS		○			○				
	Breastfeeding status					○		○	○	
	Breastfeeding process					○				
	Behavioral changes (attitude, knowledge)		○					○	○	
	User-friendliness of devices							○	○	
	Desire to continue using IoT after end of study								●	

○ Both groups, ● intervention group only

If there are missing data, the research coordinator at each site and trial secretariat will contact the participants. Data from the weight and body composition monitor, activity and sleep tracker, and online questionnaires will be stored on the Internet server. The data file will be secured with a password, and access to information will be limited to designated members such as the researchers and the trial secretariat. Paper-based documents such as consent forms will be stored at each site.

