### Allocation

Randomization will be conducted on the site level, not on the patient level. Every day during the enrollment period before starting recruitment, the trial secretariat will perform central allocation with a random number table to decide whether to enroll the participants in the intervention or non-intervention group at each site and, subsequently, will inform every site.

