### Blinding

According to the nature of the intervention, the participants and research coordinator at each site will not be blinded to the allocation. However, the physician at each site will be blinded to the allocation.

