### Subgroup analysis

The following subgroup analyses will be performed on the primary and secondary endpoints (pregnancy outcomes, body weight, body fat, blood pressure, impaired glucose tolerance, EPDS, diet, health, and breastfeeding):• Among those who will perform ≥ 80% or < 80% of measurements of body weight, body composition, and activity throughout the study period• Among those who will perform ≥ 80% or < 80% of measurements of body weight and body composition throughout the study period• Among those who will use the activity tracker for ≥ 80% or < 80% of the study period• Among those who will perform ≥ 60% or < 60% of measurements of body weight, body composition, and activity throughout the study period• Among those who will perform ≥ 60% or < 60% of measurements of body weight and body composition throughout the study period• Among those who will use the activity tracker for ≥ 60% or < 60% of the study period• Among those with body weight at registration ≥ / < the median• Among those with body composition measurement at registration ≥ / < the median• Among those with activity tracker measurement at registration ≥ / < the median

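### The median split on tracker activity at registration uses a value recorded after allocation and after the application has started, so it is not a baseline subgroup

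*Protocol article*

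**What the plan says.** The Subgroup analysis section of the protocol article lists nine splits to be applied to the primary and secondary endpoints. The last is "Among those with activity tracker measurement at registration", divided at the median.

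Five statements fix when that measurement is taken:

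- Allocation: "Every day during the enrollment period before starting recruitment, the trial secretariat will perform central allocation with a random number table", after which each site is told which group it is enrolling into.
- Blinding: "the participants and research coordinator at each site will not be blinded to the allocation".
- Intervention, on the devices: "The following IoT devices will be distributed to all participants", and the list that follows includes the fitness tracker.
- Intervention, on the start: "The intervention will be initiated on the day consent is provided during pregnancy to 1 year postpartum". Its first component is "automatically generated advice based on data (weight, body composition, activity, sleep) measured using IoT devices".
- Data collection: all participants "track their activity and sleep patterns for 1 week at the beginning of the study", and again at 6, 12 and 24 months postpartum.

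Table 1 marks the first activity and sleep measurement (both groups) and the first application use (intervention group only) in the same start-of-trial column. Registration is marked in the earlier consent column.

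**The concern.** A subgroup comparison keeps the protection of randomisation only if the splitting variable cannot respond to treatment. The label at registration suggests a pre-treatment characteristic, but the schedule describes a week of tracking that runs while one arm receives advice generated from those same tracker readings and the other does not.

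If that advice, or simply knowing the allocation, changes activity in the first week, the women above the median differ in kind between the arms. Some intervention women are there because of the application, whereas control women are there because of their usual activity. The weight difference within each half then mixes the treatment effect with that imbalance.

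**Working it through.** **Timing.** Allocation comes before recruitment on the day, so anything measured after consent is post-allocation. The trial hands out the trackers, so no study-tracker value exists before enrolment. The intervention starts on the consent day, and the first tracking window lasts a week. The article describes no run-in and no delayed activation of the application. The value called registration in the subgroup list therefore falls at or after the start of treatment.

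**Inputs from the Sample size section.** Weight change of -2% against -5%, a difference of 3 points; SD 8; two-sided 5%; 80% power; 226 evaluable women. Check: 2 × (1.960 + 0.842)² × (8/3)² = 111.6, so 112 per arm. The t-test version gives 112.6, so 113 per arm and 226 in total. The plan's figure reproduces.

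**Assumed inputs (not in the documents).** First-week shift d of 0.2 or 0.5 SD in the intervention arm; correlation ρ between usual activity and weight loss of 0.2 or 0.3; a constant true effect of -3 points in every woman.

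**Model.** Usual activity U is standard normal in both arms. The recorded value is U in controls and U + d in the intervention arm, so the pooled median is d/2. Controls fall in the upper half if U > d/2, intervention women if U > -d/2.

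Share in the upper half:
- d = 0.2: intervention Φ(0.1) = 54%, control 46%.
- d = 0.5: intervention Φ(0.25) = 60%, control 40%.

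Difference in mean U (intervention minus control), upper half: φ(d/2)/Φ(d/2) - φ(d/2)/[1 - Φ(d/2)].
- d = 0.2: 0.3970/0.5398 - 0.3970/0.4602 = 0.7353 - 0.8626 = -0.1273.
- d = 0.5: 0.3867/0.5987 - 0.3867/0.4013 = 0.6458 - 0.9636 = -0.3177.

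In the lower half the two terms change sign and swap places, which gives the same -0.1273 and -0.3177.

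Distortion of the weight effect in each half = |difference in U| × ρ × 8:

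| d | ρ | Distortion (points) | Effect seen in each half |
|---|---|---|---|
| 0.2 | 0.2 | 0.20 | -2.80 |
| 0.2 | 0.3 | 0.31 | -2.69 |
| 0.5 | 0.2 | 0.51 | -2.49 |
| 0.5 | 0.3 | 0.76 | -2.24 |

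A simulation of 2,000,000 records with ρ = 0.3 agrees. Upper and lower halves show -2.98 and -2.98 with no shift, -2.70 and -2.68 with d = 0.2, and -2.22 and -2.23 with d = 0.5.

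**Against sampling error.** Half of 226 is 113 women, about 56.5 per arm. SE = 8 × √(2/56.5) = 1.5 points, and the 95% half-width is 1.96 × 1.5 = about 3.0 points. The distortion is roughly a tenth of that or less for d = 0.2, and about a quarter in the largest case shown.

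**The case against.** The case for leaving this alone has weight. The shift and the correlation are both assumed, and one week of an application may change activity very little. Under the model the distortion is the same in both halves, so the contrast between subgroups, which is the usual purpose of a subgroup analysis, is not biased. Six of the other splits use device use throughout the study, so they are openly post-randomisation, and correcting this one does not repair them. A shared table column also does not order events within it, and Figure 2, the study timeline, could not be read for this review. If it shows the tracker week completed before the application is activated, the application could not have affected the value. All of this limits the size of the point. None of it makes the first-week value pre-treatment on the text as written.

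Two stronger readings are tempting, and the article supports neither.

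- A reader might infer that first-week steps and sleep serve as a baseline to be subtracted or adjusted for, which would remove part of the effect. Analysis of secondary outcomes plans only group means, confidence intervals and t-tests for continuous variables, with no change score or adjustment for steps or sleep. The Registration column of Table 2 also marks application logins and adherence, so it cannot mean untreated values throughout.
- A reader might infer that the diet analysis is biased, because "The same analysis will be performed to analyze changes from the start of the study to 6 and 12 months postpartum" and the first entries are made in the application itself. Diet is summarised in the intervention group only, so there is no between-arm comparison to bias.

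**Conclusion.** The point holds for one exploratory subgroup. On the article's own schedule, the tracker value used for the median split is recorded after allocation, in unblinded women, and after the application has started. The comparisons within its two halves are therefore not fully randomised. Under the assumed inputs, each half's effect is attenuated by about 0.2 to 0.8 points out of 3. The direction rests on the application raising activity and on more active women losing more weight; if either ran the other way, the distortion would reverse.

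It would be wrong to conclude that the split manufactures effect modification, since under this model it does not. It would also be wrong to conclude that the main result is at risk: the primary model adjusts for self-reported pre-pregnancy weight and does not use the tracker value.

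**What to change.** In the Subgroup analysis section, do one of the following:

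- delete the split on activity tracker measurement at registration; or
- replace the splitting variable with exercise habits from the background and lifestyle questionnaire, which both groups already complete at the start of the study, and state that it must be completed before the application is used.

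The second option needs the order of events to be known. Where it cannot be shown that the questionnaire came first, deletion is safer. Neither option changes the start of the intervention, the data collected or the primary analysis. The cost is a wording change and the loss of one exploratory device-based subgroup; the questionnaire split would rest on self-report.
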